## Abstract

**Background:**

Emotional behavior problems (EBP) are the most common and persistent mental health issues in early childhood. Early intervention programs are crucial in helping children with EBP. Parent–child interaction therapy (PCIT) is an evidence-based therapy designed to address personal difficulties of parent–child dyads as well as reduce externalizing behaviors. In clinical practice, parents consistently struggle to provide accurate characterizations of EBP symptoms (number, timing of tantrums, precipitating events) even from the week before in their young children. The main aim of the study is to evaluate feasibility of the use of smartwatches in children aged 3–7 years with EBP.

**Methods:**

This randomized double-blind controlled study aims to recruit a total of 100 participants, consisting of 50 children aged 3–7 years with an EBP measure rated above the clinically significant range (T-score ≥ 60) (Eyberg Child Behavior Inventory-ECBI; Eyberg & Pincus, 1999) and their parents who are at least 18 years old. Participants are randomly assigned to the artificial intelligence-PCIT group (AI-PCIT) or the PCIT-sham biometric group. Outcome parameters include weekly ECBI and Pediatric Sleep Questionnaire (PSQ) as well as Child Behavior Checklist (CBCL) obtained weeks 1, 6, and 12 of the study. Two smartphone applications (Garmin connect and mEMA) and a wearable Garmin smartwatch are used collect the data to monitor step count, sleep, heart rate, and activity intensity. In the AI-PCIT group, the mEMA application will allow for the ecological momentary assessment (EMA) and will send behavioral alerts to the parent.

**Discussion:**

Real-time predictive technologies to engage patients rely on daily commitment on behalf of the participant and recurrent frequent smartphone notifications. Ecological momentary assessment (EMA) provides a way to digitally phenotype in-the-moment behavior and functioning of the parent–child dyad. One of the study’s goals is to determine if AI-PCIT outcomes are superior in comparison with standard PCIT. Overall, we believe that the PISTACHIo study will also be able to determine tolerability of smartwatches in children aged 3–7 with EBP and could participate in a fundamental shift from the traditional way of assessing and treating EBP to a more individualized treatment plan based on real-time information about the child’s behavior.

**Trial registration:**

The ongoing clinical trial study protocol conforms to the international Consolidated Standards of Reporting Trials (CONSORT) guidelines and is registered in clinicaltrials.gov (ID: NCT05077722), an international clinical trial registry.

## Introduction

Externalizing behaviors are the most common and persistent mental health issues in early childhood. It is estimated that nearly 25% of preschool-aged children struggle with psychosocial stress and social-emotional issues [1]. Between 15 and 34% of young children are reported to have significant early externalizing behavior problems (EBP) such as aggression, oppositional behaviors, problems with concentration, and impulsivity [2], as measured by ECBI (Eyberg Child Behavior Inventory) [3]. If EBP symptoms that emerge at a very young age are untreated, ongoing impairments persist throughout development and with ensuing negative outcomes such as academic and legal difficulties, violent behaviors and significant mental health issues, and substance abuse [4–6]. Disruptive behavior disorders and EBP in preschool are also the most common reason for referral to specialty mental health clinics [7]. Early intervention programs that are evidence-based and easy to implement are crucial in helping young children with EBP [8].

Children with externalizing problems often display both physical (fighting with peers, hitting, kicking) and emotional (struggles with angry and aggressive feelings) symptoms. Both physical and emotional displays distract them from their learning, as well as ability to make social connections. Children with EBP are less engaged in their relationship with their parents who mostly resort to nagging them about their behaviors and lack of compliance. Problems observed in daycare and preschool are often associated with poor academic performance. Externalizing behaviors distract from the ability to complete certain required academic tasks [9].

In clinical practice, parents consistently struggle to provide accurate characterizations of EBP symptoms (number, timing of tantrums, precipitating events) even from the week before in their young children. They also are frequently unsure how their child slept. Rating scales assist parents with the recall, but they are not always reliable. Child behavior often differs depending on the situation and setting. In addition, different informants may elicit different behaviors from the same child, they may differ in their opinions regarding what is considered a significant tantrum and what is not, and they also may interpret the same behavior in different ways [10]. Clinicians rely on a brief period of observation of the child in an artificial environment of their office that is not always reflective of the child’s behavior at home and/or school. These factors contribute to suboptimal outcomes in terms of diagnosis of young children emotional and behavioral problems. This is problematic as EBP is common, starts early in life, and can often lead to significant disabilities [11]. Our ongoing program of research, and the clinical trial described by these protocol manuscripts, proposes the use of wearable-augmented prediction technology, such as smartwatches coupled with artificial intelligence (AI) to predict onset of child’s disruptive behavior and foster better parenting practices. This in turn would enable the clinician to design an individualized treatment plan based on real-time information about the child’s behavior.

### The need for wearables in promoting parenting practices

PCIT (parent–child interaction therapy) is one of the four behavior parent training (BPT) programs that are considered “well supported by research evidence” by the California Evidence-Based Clearinghouse for Child Welfare [11]. It is a dyadic parent–child therapy technique that is unique due to its utilization of in vivo parent coaching via bug-in-the-ear treatment from a therapist behind one-way glass. Most importantly, PCIT allows for individually tailored coaching that can address personal difficulties of parent–child dyads. A recent meta-analysis of the effectiveness of PCIT, focused mainly on modifications, study design, and bias, showed that PCIT was superior not only in comparing case/control groups for reducing externalizing behaviors but also in helping with parent- and child-related stress [12]. The review additionally showed that PCIT effectiveness was not affected by session length, various settings (academic versus community), or presenting problems (disruptive behaviors alone as compared to other problems complicated by disruptive behaviors). Moreover, PCIT’s unique focus on goal criteria makes the components of PCIT ideal for modifications [12].

Despite PCIT effectiveness, high dropout rates (in some studies as high as 50%) prior to completion of the treatment remain a significant problem [13]. Currently, there are some efforts to reduce high attrition by the use of new technologies such as telehealth which remotely delivers real-time therapy to the patient’s home [14]. Another significant challenge lies in the ability to frequently engage and remind parents of the parenting practices taught during PCIT sessions [15]. The current study aims to examine and facilitate further development of an innovative artificial intelligence PCIT (AI-PCIT) protocol augmented with wearable technologies such as smartwatches.

Wearable technologies such as smartwatches allow for objectively measuring activities that extend beyond observations reported in the clinical settings. Wearables have been tested for continuous monitoring during pregnancy [16] and promoting physical activity in adolescents with juvenile idiopathic arthritis [17]. Despite the clinical need, wearable technologies have not been widely studied nor implemented for the treatment of young children with EBP.

### Objectives

The overall objectives of this AI-PCIT treatment clinical trial are to evaluate feasibility of the use of wearables such smartwatches: in children aged 3–7 years with emotional behavioral problems (EBP). We hypothesize that children with EBP undergoing PCIT will adhere to and tolerate wearables (e.g., Garmin vivosmart4 smartwatch) by having at least 70% of enrolled patients being able to wear it 70% of their treatment period. This will be monitored by checking sleep, heart rate, and intensity of data obtained from Garmin watches. The study will also evaluate the effectiveness of AI-PCIT by comparing weekly behavioral treatment outcomes as compared with control group over a 12-week period. The study will also serve to track indirect behavioral measures on smartwatches (i.e., measurements of heart rate, intensity of activity) from young patients as compared to parental rating scales of ECBI (obtained weekly). These measures can then be used for target engagement biomarkers in future interventional trials. Finally, we will also collect whole blood from both child and parent to investigate exploratory analyses on biomarkers (e.g., C-reactive protein, metabolomics, exposomics) of response to PCIT.

## Methods

Our clinical trial is examining the AI-PCIT for treatment of externalizing behavioral problems in young children. Participants are recruited from Young Child Behavioral Clinic (YCBC) at Mayo Clinic in Rochester, MN, USA, and through advertisements at local pediatrics and family medicine clinics. Interested participants are initially provided information about the study and are scheduled for a consult in the Young Child Behavioral Clinic. The overall recruitment goal for the trial is *N* = 50 participants between ages of 3–7 years whose measure of EBP rated above the clinically significant range (T-score ≥ 60) (Eyberg Child Behavior Inventory-ECBI; Eyberg & Pincus, 1999) [3]. Participants are randomly assigned to AI-PCIT group or PCIT-sham biometric group. Each child is recruited with their parents who are at least 18 years old for a total recruitment of 100 participants. Participants are children aged 3–7 years old. They are of any gender, race, or ethnicity recruited from outpatient or inpatient care. Inclusion criteria include the patients’ ability to provide developmentally appropriate informed assent and legal guardians that are able to provide informed consent. Furthermore, the patient’s EBP severity must be rated above the clinically significant range (≥ 120; T-score ≥ 60) (Eyberg Child Behavior Inventory-ECBI; Eyberg & Pincus, 1999) [3]. The need for more intensive behavioral treatments such as an ER visit or hospitalization for behavioral dyscontrol will not be exclusionary or exit criteria. Participants must be fluent in the English language, have verbal abilities, and have the competency to consent based on ability to provide a spontaneous narrative description of the key elements of the study. Participants also require at least one smartphone and Internet access. Exclusion criteria for the PISTACHIo clinical trial include individuals who are unable to speak and understand English; patients who refuse or withdraw their consent, or those who are unable or unwilling to adhere to study procedures; and patients who do not have a smartphone and access to Internet connection. The study has the approval of the local institutional review board for human subject research protection (Mayo Clinic, Rochester, MN, USA).

### Baseline clinical and functional assessment before PCIT treatment

Caregivers will be interviewed using the Kiddie-Schedule for Affective Disorders and Schizophrenia-Early Childhood (K-SADS-EC) which is administered to assess the child’s psychiatric symptoms and assign DSM-5 diagnoses along with the Preschool Age Psychiatric Assessment (PAPA), a reliable measure of Axis I disorders (and severity) in preschool children, (Egger et al., 1999; Egger et al., 2006) [18, 19]. Children’s Global Assessment Scale (CGAS) is completed by the clinician rater to measure children’s global level of impairment. Parenting Stress Index (PSI) is used to measure the magnitude of stress within the parent–child dyad via caregiver report. Coping with children’s negative emotions (CCNES) is used to assess parental coping styles and strategies in response to children’s expression of negative emotions via caregiver report. To capture a wider range of problematic behaviors, this study uses the Child Behavior Checklist (CBCL). Preschool Feelings Checklist (PFC) is used to quickly screen for the presence of any symptoms of depression in our population. The Pediatric Sleep Questionnaire (PSQ) is used to examine sleep behavior in young children. Trauma Symptom Checklist for Young Children (TSCYC) is used for the assessment of trauma-related symptoms in children ages 3–12. Finally, the Early Childhood Screening Assessment (ECSA) is used to identify very young children (1½–5 years old) who need further emotional or behavioral assessment.

Children and parents (one primary caregiver) who qualify and agree to participate in the study are given vivosmart4 smartwatches during their screening/baseline assessment visit. Two external service providers are used for aggregating Garmin-collected smartwatch data (Fitabase, cloud-based product of Small Steps Labs LLC) and to deliver real-time alerts for parents and collect daily/weekly behavioral functioning of study’s children (mEMA: mobile Ecological Momentary Assessment, a mobile application product of Ilumivu). Deidentified subject identifiers (IDs) are used to create accounts for Fitabase and mEMA, thereby no protected health information (PHI) of the patient is made available to any external data aggregation or alert service providers. Data is collected and stored throughout the study which is then analyzed at study closure. Data from Garmin vivosmart4 smartwatches are automatically synced to Garmin Connect via participant’s smart device (e.g., smartphone, tablets) and to Ilumivu’s mEMA smartphone app. Each update on Garmin Connect updates the data in Fitabase as well. Ilumivu’s mEMA app, available on iOS and Android app stores, serves to trigger assessments in an attempt to foster parenting practices based on child’s physiology. Optional blood tests (only if patients and primary caregivers upon providing consent) are collected for exploratory work and ongoing collaborations in our local lab.

### Study procedures

The PISTACHIo clinical trial utilizes a randomized, double blind, design to compare the active PCIT-AI group and PCIT-sham (treatment as usual) group. The child and primary caretaker are fitted with Garmin watches that are required to be worn for a minimum of 70% of the days during their 12 weeks of treatment. In addition to this, we require the participants to wear the watch for at least 70% of every 24 h per the principal investigator’s discretion. Families are scheduled for PCIT treatment with PCIT-certified therapist in the Young Child Behavioral Clinic. Before the first PCIT treatment session, all participants are randomized into an active versus sham arm of the study. This is done by using a computer-generated list based on a stratified randomization scheme and using a permuted block method with a random number generator. The research assistant, research coordinator, and computer engineer who monitors Garmin apps are the only team members aware of which group the participant belongs to (active vs sham) [20]. Study investigators, clinical/cognitive raters, and participants are blind to the treatment condition. Parents in the AI-PCIT group are receiving targeted messages that instruct them on how to de-escalate their child when the Garmin device recognizes vital signs associated with a child’s tantrum. Parents in the PCIT-sham group receive random messages throughout the day with various relaxation strategies such as reminders to practice deep breathing with their child. The treatment is overseen by board-certified child and adolescent psychiatrist who is a Within-Agency PCIT Trainer.

Any participants withdrawn from the study if they were non-adherent to study procedures or met exclusion criteria at any point after the consent will not be replaced, and their data will not be used for analysis. Additionally, broken watches will be replaced, and therefore, the participant will not be excluded from the study.

The ongoing clinical trial study protocol conforms to the International Consolidated Standards of Reporting Trials (CONSORT) guidelines and is registered on Oct 14, 2021, in clinicaltrials.gov (ID: NCT05077722), an international clinical trial registry. See Fig. 1 depicting the PISTACHIo study workflow and timing for study procedures.

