### Proposed analysis

This study is an exploratory clinical trial with the broad goals of demonstrating feasibility, producing pilot data, generating validate effect sizes, and informing future larger, multicenter trials. The level of significance will be set at *α* = 0.05 (two tailed), and to address multiple testing (where applicable), *p*-values will be adjusted using the false discovery rate. We estimated the sample size for this pilot study based on the hypothesis examining clinical outcome (ECBI) between the PCIT-AI group and PCIT-sham group (hypothesis 2a). We anticipate that a sample size of 50 participants per group (*N* = 100) achieves 70% power, at a 0.05 alpha level (two tailed) to detect an odds ratio of 2.0 favoring PCIT-AI with the proposed randomized design. To evaluate feasibility of the use of Garmin wearables, we will use descriptive statistics assessing the frequency of Garmin use in participants (70% or greater is defined as success for this hypothesis). A linear mixed model analysis of repeated measures will be used to evaluate the interaction effects of type of PCIT (AI informed or AI sham), time, and ECBI scores. A separate linear mixed model analysis will be used to evaluate the interaction effects of PCIT type (AI informed or AI sham), time, and PSQ scores with ECBI scores as a covariate. To evaluate concordance of sleep cycle data from children aged 3–7 as compared to parental rating scales of PSQ, we will use Spearman correlation coefficients and mixed linear regression models. Separate Spearman correlations and a mixed linear regression model will examine the relationship between biometric data from smartwatches (heart rate and movement) with weekly ECBI reports. Partial least-square regression networks will be used to derive multi-omic integration networks, and Spearman correlation will then be used to associate omics with physiological measures from smartwatches.

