## Discussion

Currently, there are no AI-augmented treatments for young children with EBP. PCIT is an evidence-based behavioral treatment for 3–7 years old with EBP supported by numerous meta-analyses studies [12, 34, 35]. Attrition rates in PCIT are high and can reach 25 to 69% depending on the study [13, 36]. Factors such as education, income, family employment, and parents’ engagement have been cited as main reasons for attrition [37].

Our study is first to offer AI-augmented PCIT treatment for young children with EBP which will allow for improved engagement of families. The main goal of PCIT is to strengthen the relationship between the parent and child. With the use of our Garmin technology, we can augment that goal by sending targeted messages to parents in critical moments when their child needs help. What is particularly innovative about our project is that the chosen smartwatch does not require the young child to spend time in front of a screen or to interact with an app, both situations that many parents are opposed to for children of this age range. Instead, it helps parents to remember important therapy techniques during real-world parent/child interactions which can be vital learning opportunities for the dyad.

Our study additionally provides us with a valuable environment to test the relationship between multi-omic associations of disruptive behaviors in a parent–child dyad and associations with physiological smartwatch measures. This has never been studied in children with EBP.

It is important to note that data privacy is a significant concern in mobile health, particularly in the research area. As a procedure at enrollment, the study team disengages location, calendar, contacts, social media, and microphone settings on the Garmin Connect and mEMA applications. However, the study will not stop participants from using their discretion to change these settings should they choose to utilize additional features commodity smartwatches provide. Additionally, all self-reported assessments through the mEMA application are deidentified as the connection between the application, and the Ilumivu website is done through a randomly generated code accessed by IRB-approved study personnel.

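### The rule that discards data of participants withdrawn for non-adherence can remove non-wearers from the endpoint that measures wear, and conditions the randomised comparison on post-randomisation behaviour

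*Protocol article*

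**What the plan says.** All references are to the protocol article.

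- **Aim (Abstract, Background).** "The main aim of the study is to evaluate feasibility of the use of smartwatches in children aged 3–7 years with EBP".
- **Success criterion (Objectives).** The hypothesis is tolerance shown by "having at least 70% of enrolled patients being able to wear it 70% of their treatment period". The denominator is enrolled children.
- **Analysis of that criterion (Proposed analysis).** "descriptive statistics assessing the frequency of Garmin use in participants (70% or greater is defined as success for this hypothesis". Here the denominator is only participants; it is not tied to enrolment.
- **Wear as a study procedure (Study procedures).** Child and caregiver receive "Garmin watches that are required to be worn for a minimum of 70% of the days during their 12 weeks of treatment", and are also required to "wear the watch for at least 70% of every 24 h per the principal investigator’s discretion".
- **Exclusion criterion (Methods).** The exclusions include "those who are unable or unwilling to adhere to study procedures".
- **Data rule (Study procedures).** Participants withdrawn for not adhering to procedures, or because they "met exclusion criteria at any point after the consent will not be replaced, and their data will not be used for analysis".

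Study procedures places randomisation before the first PCIT session. The section on baseline assessment has watches handed out at the screening/baseline visit. A broken watch is replaced and does not lead to exclusion. No other exception to the data rule is given.

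**The concern.** The wear threshold does two jobs. It is the yardstick for the main aim, and it is an obligation whose breach is a possible ground for withdrawal. Once a non-wearer is withdrawn, the data rule takes that child out of the analysis. The Objectives criterion would count the same child as enrolled and not adherent. Both statements cannot be followed for such a child unless the feasibility analysis is exempt from the rule, and the article does not say that it is. The 70% mark could then be reached partly because children who failed it are no longer counted.

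The second issue is the comparison of AI-PCIT with sham. Adherence over the 12 treatment weeks comes after randomisation, and the arms receive different messages. The Discussion expects AI-PCIT to improve family engagement and names parental engagement among the reasons for attrition. The rule therefore selects children for the ECBI and PSQ models on behaviour that the intervention may affect. It also discards weekly scores already collected before withdrawal, which the planned mixed model could use.

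**Working it through.** **Inputs from the article.** 50 children (Abstract, Methods); success at 70% or more. This means 0.70 × 50 = 35 children. The article gives no expected adherence, no expected share of non-adherers withdrawn and no outcome gap, so every such value below is an assumption.

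**1. Feasibility, removal of non-adherers only.** Let t be the true share adherent and f the share of non-adherers withdrawn.

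Reported rate = t / [t + (1 − t)(1 − f)]

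Setting this to 0.70 gives f = 1 − 0.3t / [0.7(1 − t)]:
- t = 0.5: f = 1 − 0.15/0.35 = 0.57
- t = 0.6: f = 1 − 0.18/0.28 = 0.36

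In whole children out of 50:

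| Assumed adherent | All enrolled counted | One withdrawal short | Enough withdrawn | All non-adherers withdrawn |
|---|---|---|---|---|
| 25 | 25/50 = 50% | 14 of 25: 25/36 = 69.4% | 15 of 25: 25/35 = 71% | 25/25 = 100% |
| 30 | 30/50 = 60% | 7 of 20: 30/43 = 69.8% | 8 of 20: 30/42 = 71% | 30/30 = 100% |

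With f = 1 the reported rate is 100% at any true rate.

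**2. Chance of declaring success.** Take K adherent children as binomial (50, t), and W withdrawn non-adherers as binomial (50 − K, f). The probability that K/(50 − W) is at least 0.70, for an assumed t = 0.6, is:
- f = 0: 9.6%
- f = 0.25: about 32%
- f = 0.5: 78%
- f = 1: 100%

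**3. Feasibility, removal in the other direction.** The rule also covers other procedures and other exclusion criteria, such as withdrawn consent or no smartphone or Internet access. If 5 of 30 wearers were removed for such reasons and no non-wearers were, the rate would be 25/45 = 56% instead of 60%.

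**4. Randomised comparison.** Let p be the share removed in an arm and d the amount, in SD, by which removed children do worse than retained ones. The retained mean is then better than the arm's full mean by p × d, so

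Bias = p(AI) × d(AI) − p(sham) × d(sham)

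- Equal p and equal d: 0.
- 25% versus 50% removed, d = 0.5 in both arms: 0.25 × 0.5 = 0.125, about 0.13 SD.
- 25% versus 50% removed, d = 1.0 in both arms: 0.25 × 1.0 = 0.25 SD.

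The arm that loses more children looks better than it is. If the alerts do improve engagement, the sham arm would lose more and the bias would run against AI-PCIT.

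A second illustration takes no treatment effect, with 60% retained in one arm and 80% in the other. The extra 20% retained do worse by 0.3 to 0.8 SD. The retained arms then differ by 0.2 × 0.3/0.8 = 0.075 SD to 0.2 × 0.8/0.8 = 0.20 SD. For a simple two-sided 5% comparison of means, the type I error becomes about 6 to 9% with 25 randomised per arm (15 and 20 retained).

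**The case against.** The strongest reply has four parts.

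**No trigger is stated.** The data rule says what happens to withdrawn participants, not who is withdrawn. The 24-hour requirement is left to the principal investigator's discretion, and the smartwatch section speaks of encouraging wear. A reader might infer that low wear automatically leads to withdrawal; the article does not say so. This stands, and it limits the point to saying that the feasibility result can be partly circular. It does not rescue the rule: discretion over who leaves the denominator makes the rate harder to interpret.

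**The direction is not fixed.** A reader might infer that feasibility is always biased upwards. That holds only for removal of non-wearers; step 3 shows the reverse. Upward bias is the more plausible direction, but it is not certain.

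**The size is not known.** A reader might apply the Discussion's background figure ("Attrition rates in PCIT are high and can reach 25 to 69% depending on the study") and conclude that 19 down to 8 children per arm would be analysed. The article does not support that. The figure describes treatment attrition in other PCIT studies, not withdrawal with data removal under this rule, and the calculation needs 25 children per arm whereas Proposed analysis speaks of 50 per group. Nor does it follow that the randomised comparison is necessarily distorted: with equal removal and equal gaps the bias is zero, and the type I error in the second illustration rises only modestly.

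**This is an exploratory pilot, and analysis sets are usually detailed elsewhere.** True, and a full protocol or SAP may define them. But the article does not leave the matter open. It states a rule, exempts neither feasibility nor the outcome models, and conflicts with its own enrolled denominator. One could read the rule as dropping a withdrawn child's data while still counting the child as an enrolled failure. If that is meant, it has to be written.

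**Conclusion.** The point holds. Applied as written, the data rule lets children who do not tolerate the watch leave the endpoint that measures tolerance, and it conflicts with the criterion in Objectives. For feasibility, withdrawing 15 of 25 non-adherers (25 of 50 adherent) or 8 of 20 (30 of 50 adherent) turns a clear failure into a 71% pass. These adherence figures are assumed, and the illustrations have no wearers removed. The net effect in the trial depends on who is withdrawn and why, which the article does not fix.

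For ECBI and PSQ, the rule selects on post-randomisation behaviour that the alerts may influence. The bias ranges from zero under equal removal and equal gaps to about 0.13 to 0.25 SD under the assumed 25% versus 50% removal and a gap of 0.5 to 1.0 SD. Both conclusions may therefore be biased; the article does not show that they will be. Because one sentence affects both the main aim and the efficacy comparison, it should be changed before any analysis.

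**What to change.** Replace the data rule with the following.

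1. **Feasibility.** The denominator is every enrolled child given a watch. A child who is withdrawn or does not reach the wear threshold counts as not meeting the criterion. Enrolment is the right starting point, because watches are issued at the screening/baseline visit and a child who rejects the watch before randomisation would be lost from a randomised denominator. Use the same denominator in Objectives and Proposed analysis.
2. **ECBI and PSQ.** Analyse all randomised children as randomised in the planned mixed models. Use every score collected up to withdrawal and, where consent continues, the weekly parent forms collected after the watch is no longer worn.
3. **Exclusion of data.** Exclude data only when permission to use them is withdrawn.
4. **Adherers only.** Keep this analysis, labelled as supportive.

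The cost is a change of protocol and analysis wording, plus continued collection of parent forms that already exist. The downside is that the feasibility rate may look less favourable.

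### The bar on replacing participants starts at consent, but randomisation comes later; the plan should say that the 50 are randomised children and start the bar at randomisation

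*Protocol article*

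**What the plan says.** All references are to the protocol article.

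- **Replacement rule (Study procedures).** It covers participants withdrawn for non-adherence and those who "met exclusion criteria at any point after the consent will not be replaced, and their data will not be used for analysis". It therefore starts at consent and does two things: it bars replacement and it removes data.
- **Timing of randomisation (Study procedures).** "Before the first PCIT treatment session, all participants are randomized into an active versus sham arm of the study".
- **A step before treatment (Baseline clinical and functional assessment before PCIT treatment).** Children and one caregiver who qualify and agree "are given vivosmart4 smartwatches during their screening/baseline assessment visit". The same section lists the baseline assessments.
- **Exclusion criteria (Methods).** They include "patients who refuse or withdraw their consent, or those who are unable or unwilling to adhere to study procedures". A family can meet these after consenting and before being assigned to an arm.
- **Size (Methods; Abstract).** "The overall recruitment goal for the trial is" 50 children. Parents are counted as well: "Each child is recruited with their parents who are at least 18 years old for a total recruitment of 100 participants". Neither section says whether the 50 are consented or randomised children.
- **Feasibility aim (Objectives).** Success means that at least 70% of enrolled patients wear the watch for 70% of the treatment period.

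**The concern.** Not replacing participants is sound practice after randomisation, because filling an emptied place in an arm can disturb the balance that randomisation created. Before randomisation a family belongs to no arm, so replacing it cannot bias the comparison. A rule that starts at consent thus gives up sample size in that interval and gains nothing.

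Two things are at stake. One is the number randomised, in a trial of only 50 children. The other is the meaning of the wear rate. The rule also discards the data of families who leave, so a child who is enrolled, receives a watch and refuses it early can disappear from a proportion whose stated base is enrolled patients.

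**Working it through.** **1. Can the rule apply before randomisation?** The rule runs from consent. Randomisation is fixed only as some time before the first session. Withdrawing consent and being unwilling to adhere are both exclusion criteria. Nothing limits the rule to randomised families, so it can apply before randomisation.

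**2. The plan's own size statement.** Proposed analysis states: "We anticipate that a sample size of 50 participants per group" (N = 100) "achieves 70% power" for an odds ratio of 2.0 at two-sided alpha 0.05. I used the usual two-proportion formula, with n per arm and p̄ the mean of p1 and p2:

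power = Φ{ [|p2 − p1| − 1.96·√(2p̄(1 − p̄)/n)] / √([p1(1 − p1) + p2(1 − p2)]/n) }

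The control rate is not given, so I scanned it from 0.01 to 0.99. With 50 per arm, the highest power at any control rate is 40.2% (control rate about 0.41), so the 70% is not reproduced. Moreover, 100 participants are 50 child–parent pairs, or about 25 children per arm if allocation is 1:1, where the highest power is 22.4%. That mismatch is a separate matter. Here it shows only that the sample has no reserve to absorb early losses, and the power statement mentions no allowance for any.

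**3. Number randomised under an assumed loss.** The documents give no pre-randomisation loss rate; 10% and 20% are assumptions. If the 50 are consented families, the number randomised is 50 × (1 − loss). The standard error of an arm difference scales with 1/√N.

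| Loss before randomisation | Children randomised | Standard error ratio | Highest power, odds ratio 2.0 | Power, standardised difference 0.497 | Consents needed to randomise 50 |
|---|---|---|---|---|---|
| 0% | 50 | 1 | 22.4% | 41.9% | 50 |
| 10% | 45 | √(50/45) = 1.054 | 20.6% | 38.5% | 50/0.9 = 55.6, so 56 |
| 20% | 40 | √(50/40) = 1.118 | 18.7% | 34.9% | 50/0.8 = 62.5, so 63 |

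The value 0.497 is the standardised difference that gives 70% power at 50 per arm: (1.960 + 0.524) × √(2/50) = 0.497. It is included because ECBI is analysed with a linear mixed model. Power is Φ(0.497·√(n/2) − 1.96), with n = 25, 22.5 and 20 per arm. Each 10% lost costs 5 children and about 2 to 4 percentage points of power.

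**4. The wear rate.** Suppose 50 children are enrolled and issued watches, and those who leave early count as non-wearers. If 5 are dropped from the data, the 70% target needs 0.70 × 45 = 31.5, so 32 wearers; out of all 50 enrolled, 32 is 64%. If 10 are dropped, the target needs 0.70 × 40 = 28 wearers, and 28 of 50 is 56%. The trial could report success with a wear rate of 64% or 56% among enrolled children. This effect comes from the data-exclusion clause, not from the bar on replacement.

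**The case against.** The best case against the point has four parts.

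- **The 50 may already mean randomised children.** The text speaks of participants being randomly assigned and never says that a family lost early uses up a place. This stands, and it is why the point is conditional. A reader might infer that shrinkage below 50 is certain. The documents do not say so; they leave the 50 undefined beside a rule that starts at consent.
- **The interval may be very short.** Only a latest time for randomisation is given, and randomisation at the baseline visit is not ruled out. Fig. 1, which shows the timing, is not available here. With a short interval the loss would be close to nil. This also stands.
- **Early refusal of the watch is not shown to be common.** A reader might infer that refusals will surface between watch issue and randomisation. Nothing supports that: the wear requirement applies to the 12 weeks of treatment. Nor can the 25% to 69% attrition in the Discussion be used as a loss rate for this interval, because it concerns PCIT in general.
- **Lost precision in the wear rate cannot be blamed on the replacement rule.** It is tempting to say that the 95% half-width at a 70% wear rate, 1.96·√(0.7 × 0.3/n), grows from 12.7 to 13.4 or 14.2 percentage points for n = 50, 45 and 40. But the base is enrolled patients, and a family lost before randomisation may still be enrolled. The base shrinks only because data are discarded.

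It can also be said that a fixed consented cohort suits a feasibility pilot, since early exit is itself information. That would carry weight if early leavers' data were kept, but the rule discards them. Nor is this a detail left to a fuller document: the article states the starting point itself.

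**Conclusion.** The point holds in conditional form and is minor. The replacement rule starts at consent, before any arm exists. On one reading of the 50 it can reduce the number randomised for no benefit; on the other it contradicts the intended size. Either way the sentence needs correcting.

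The size cannot be established from the documents. The 5% to 12% rise in standard error rests on an assumed 10% to 20% loss and on the 50 counting consented families; the power figures also assume 1:1 allocation. In a self-described exploratory pilot, a change of that order is unlikely to alter a decision. The case for acting is that the correction is cheap and that the same sentence can distort the wear rate on which the feasibility aim is judged.

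Discarding data from randomised participants who do not adhere is a different and larger problem in the same sentence. It is not assessed here.

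**What to change.** 1. In Methods, state that the goal is 50 randomised children.
2. In Study procedures, bar replacement from randomisation onward. Replace families lost between consent and randomisation until 50 children are randomised, and report them in the participant flow.
3. Amend the data-exclusion clause so that every enrolled child issued a watch, including one who refuses it early, stays in the denominator of the wear rate given in Objectives. Without this step, replacing early refusers would itself flatter the result.

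**Cost.** The wording changes are short, but they affect the data-exclusion clause as well as the replacement clause. A few extra families would be consented and screened: about 6 to 13 more under the assumed losses (56 − 50 and 63 − 50). The reported wear rate may be lower. The planned number randomised does not rise.
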